## **8.0 Assessment of Safety**

Adverse Events will be reported, if applicable.

## **9.0 Statistical Analysis**

### **9.1 Reporting Results, Descriptive Measures**

A completed subject will have a FIT assessment, an Epi proColon assessment, and a medical diagnosis/colonoscopy determined CRC/NED status. Demographic and baseline covariates will be reported for each individual. Medical diagnosis/colonoscopy is regarded as a reference standard. FIT is regarded as a non-reference standard.

For Group A (CRC) all completed individuals with valid results will be reported in tabular form. The number of individuals considered disease positive and disease negative will be reported as determined by FIT and Epi proColon. Screen failures and incomplete cases will be provided in listings. From the tabular results the proportion (or percent) regarded as disease positive will be calculated for both FIT and Epi proColon. In both cases the numerator will be the number of test positives identified correctly by each test

(confirmed by medical diagnosis/colonoscopy) and the denominator will be the number identified by medical diagnosis/colonoscopy as disease positive. Additionally the proportion (or percent) agreement will be calculated between FIT and Epi proColon and regarded as the 'positive percent agreement' and 95% confidence intervals will be provided.

For Groups B (NED) all completed individuals with valid results will be reported in tabular form. For each group the total number of NED individuals will be reported as determined by medical diagnosis/colonoscopy for complete subjects. In tabular form the number of individuals considered disease negative and disease positive will be reported as determined by FIT and Epi proColon. Screen failures and incomplete cases will be provided in listings.

From the tabular results the proportion (or percent) regarded as disease negative will be calculated for both FIT and Epi proColon. In both cases the numerator will be the number of test negatives identified correctly by each test (confirmed by medical diagnosis/colonoscopy) and the denominator will be the number of test negatives identified by medical diagnosis/colonoscopy. Additionally the proportion (or percent) agreement will be calculated between FIT and Epi proColon and regarded as the 'negative percent agreement' and 95% confidence intervals will be provided.

Sensitivities and specificities will be calculated in the above cases where FIT and Epi proColon will be compared to medical diagnosis/colonoscopy as reference standard. Parameters estimated and 95% confidence intervals will be provided.

Listing or line data will be provided for all studies which will include a complete listing of samples with demographic information, clinical diagnosis and the results of both assays. False negatives, false positives, and nonconcordance between FIT and Epi proColon will be described in detail.

Details of data displays in tabular, listing and figure format will be detailed in the Statistical Analysis Plan as recommended in the FDA Guidance 'Design Considerations for Pivotal Clinical Investigations for Medical Devices'.

## 9.2 Statistical Inference, Sample Size

In addition to the descriptive methods described in the previous section, statistical inference will be based on sensitivity and specificity as well as positive percent agreement and negative percent agreement.

Clinical performance of Epi pro Colon and FIT will be compared in terms of:

- Sensitivity for colorectal cancer (CRC) relative to reference standard.
- Specificity for no evidence of disease (NED) relative to reference standard.

The sensitivities of Epi proColon and FIT will be compared to establish non-inferiority. Likewise the specificities of Epi proColon and FIT will be compared to establish equivalence.

Non-inferiority of the Epi proColon assessment when compared to FIT assessment will be evaluated using a McNemar's test with type I error rate 0.05. For both sensitivity and specificity differences 95% confidence intervals will be provided.

For the sample size calculation, the primary comparison of sensitivities and specificities is considered to be a non inferiority test for two correlated proportions.

With a type I error rate of 5% and 80% power a sample size of 100 subjects per Group would be required. The maximum allowable difference between the sensitivities (Epi proColon compared to FIT) and specificities (Epi proColon compared to FIT) that still results in non-inferiority (non-inferiority margin) is 0.20.

An attrition rate of 50% will be assumed. Therefore, in order to collect 100 valid samples per group, a minimum of 200 subjects will be enrolled per group.

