### **9.3 Hypothesis Acceptance / Validity Criteria**

#### **9.3.1 Sensitivity for colorectal cancer**

Test performance of the Epi proColon test is considered non-inferior to FIT in CRC subjects, if the sensitivities of Epi proColon and FIT (both relative to reference standard medical diagnosis/colonoscopy) are determined to be equivalent by showing a difference no greater than 0.20 in the two sensitivities.

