### **9.4 Additional Analyses**

Subgroup analysis will be conducted on age, race, and clinical site provided reportable numbers are available and other demographic factors collected on the case report forms. Tabular presentations will be provided showing frequency distributions and line listings will be provided separately.

Center descriptive statistics will be presented to show the effect of center. As a secondary analysis, the primary analysis will also be conducted as a superiority hypothesis test.

In addition, sensitivity and specificity will be calculated for all samples tested with Epi proColon, regardless of whether or not there is a valid FIT result.

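### Section 9.2 names McNemar's test for non-inferiority, but that test contains no margin, and the 0.20 limit in 9.3 is not tied to any test or confidence limit

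*Protocol*

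**What the plan says.** The primary objective (Protocol 3.1) is non-inferiority of Epi proColon to FIT. Four places bear on how that is decided.

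- **Named test (9.2):** "Non-inferiority of the Epi proColon assessment when compared to FIT assessment will be evaluated using a McNemar's test with type I error rate 0.05". Sidedness is not stated.
- **Sample size (9.2):** "the primary comparison of sensitivities and specificities is considered to be a non inferiority test for two correlated proportions". The largest tolerated loss "that still results in non-inferiority (non-inferiority margin) is 0.20", for sensitivity and for specificity. The result: "With a type I error rate of 5% and 80% power a sample size of 100 subjects per Group would be required".
- **Intervals (9.2):** "For both sensitivity and specificity differences 95% confidence intervals will be provided". Nothing says what a limit is to be compared with.
- **Acceptance rule (9.3.1, with the same form for specificity in 9.3.2):** the sensitivities must be "determined to be equivalent by showing a difference no greater than 0.20 in the two sensitivities".

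Section 9.4 adds that, as a secondary analysis, "the primary analysis will also be conducted as a superiority hypothesis test".

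**The concern.** A non-inferiority test must reject a null hypothesis placed at the margin, here that Epi proColon minus FIT is -0.20 or worse. McNemar's test places its null at zero. A non-significant result does not show that the loss is below 0.20. A significant result against Epi proColon does not show that the loss exceeds 0.20. A significant result in its favour is superiority, which 9.4 treats as a separate question.

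The one sentence governs both comparisons, in a study meant to support the device's safety and effectiveness for its intended use (2.2). With the test, the margin, the intervals and the acceptance rule left unconnected, the same data can support opposite conclusions, and the choice between them could be made after the results are seen.

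**Working it through.** **Inputs from the protocol:** McNemar's test at 0.05; margin 0.20; 100 evaluable pairs per group; 80% power; 50% attrition. **Not given in 9.2:** expected accuracies of the two tests, the share of discordant pairs, sidedness. These are assumed below and varied.

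**Notation.** Among n = 100 pairs in a group, b = Epi proColon only correct, c = FIT only correct; difference = (b - c)/n; ψ = true discordant share; d = true loss of Epi proColon against FIT.

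**1. The plan's own sample size.** For a paired non-inferiority test, n = (z_α + z_β)²(ψ - d²)/(0.20 - d)². With d = 0, ψ = 0.50 and one-sided 0.025, n = (1.960 + 0.842)² × 0.50/0.04 = 98.1, so 99. With one-sided 0.05, ψ = 0.50 gives 78, and about 0.65 is needed to reach 100. The figure of 100 is thus compatible with a margin-based calculation but cannot be reproduced from stated inputs alone. Enrolment of 200 = 100/(1 - 0.50) agrees.

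**2. What McNemar's test uses.** Its statistic is (b - c)²/(b + c). Neither the margin nor n enters.

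**3. Named test against margin, n = 100.** The score (Tango) interval solves (b - c - nδ)/√{n[2q + δ(1 - δ)]} = ±1.96 for δ, where q is the estimate of the FIT-only share when the difference is fixed at δ.

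| b v c | Difference | McNemar statistic and two-sided p | 95% score interval | Lower limit above -0.20? |
|---|---|---|---|---|
| 2 v 12 | -0.10 | 100/14 = 7.14, p = 0.008 | -0.182 to -0.031 | yes |
| 20 v 32 | -0.12 | 144/52 = 2.77, p = 0.096 | -0.257 to 0.022 | no |

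The simple Wald interval gives the same verdicts. Its standard errors are √(14 - 100/100)/100 = 0.0361 and √(52 - 144/100)/100 = 0.0711, so the lower 95% limits are -0.171 and -0.259. The verdicts also survive a one-sided 0.05 level: -0.10 - 1.645 × 0.0361 = -0.159 and -0.12 - 1.645 × 0.0711 = -0.237.

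**4. The 9.3 rule read as a point estimate.** At a true loss of exactly 0.20, the chance that c - b is at most 20 out of 100 is about 53% (exact enumeration, sensitivities assumed 0.50 v 0.70 with independent errors, so ψ = 0.50 × 0.30 + 0.50 × 0.70 = 0.50). The estimate is centred on the limit, so a rate of about one half is expected.

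**5. If a non-significant McNemar result were taken as non-inferiority (an assumed reading).** Exact enumeration at n = 100 and a true loss of 0.20:

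| Assumed ψ | 0.25 | 0.30 | 0.40 | 0.50 | 0.60 |
|---|---|---|---|---|---|
| Passes | 0.5% | 2% | 9% | 18% | 26% |

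A margin-based test at one-sided 0.025 passes about 2.5%. For orientation, 0.67 (the first-generation sensitivity in 2.2) v 0.87 with independent errors gives ψ = 0.67 × 0.13 + 0.33 × 0.87 = 0.37 and a pass rate of 7.2%.

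**6. The opposite direction.** With specificities of 0.89 (first-generation figure in 2.2) v 0.95 (assumed for FIT) and independent errors, the score test shows non-inferiority in 91% of trials. In 25% of all trials it does so while McNemar's test is significant against Epi proColon. If significance in favour of Epi proColon were required, two equally sensitive tests would succeed about 2.5% of the time.

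**The case against.** The best defence is that the protocol does contain a margin-based rule. It defines 0.20 as the margin, describes the primary comparison as a paired non-inferiority test, promises 95% intervals for both differences, sets acceptance at 0.20 in 9.3, and keeps superiority apart in 9.4. On this view McNemar's name is a loose label for a paired test, and an analysis plan not shown here may give the shifted statistic.

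Much of this stands. The materials for a valid decision are present, and a reader who infers that the trial cannot answer its primary question goes too far. Nor does any section say that a non-significant McNemar result counts as non-inferiority, so the pass rates under that reading are conditional, and at low discordance they are no worse than a correct test's.

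A reader might also infer that missing pairs would make a finding of no significant difference easier to reach. The documents do not support that: 4.3 and 9.5 continue recruitment until 100 complete pairs per group are obtained.

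What does not stand is the rescue itself. No section defines a margin-shifted McNemar-type test or compares a confidence limit with -0.20, and 9.3 leaves open what must not exceed 0.20. A correct analysis plan would still contradict the protocol's sentence.

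**Conclusion.** The point holds as a wrong choice of named test and a missing link between test, margin and interval. That part rests on no assumed figure: the null of McNemar's test is zero, and the two examples show disagreement with the margin in each direction at the planned 100 pairs.

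The sizes do rest on assumptions. The 53% for the point-estimate reading uses sensitivities of 0.50 v 0.70. The 0.5% to 26% range needs both the assumed reading of non-significance and discordant shares of 0.25 to 0.60; no single value in it should be quoted as the error rate of this trial. The 2.5% benchmark takes the 0.05 as two-sided, which the protocol does not state.

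The sentence should be corrected before analysis because it governs both primary comparisons.

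**What to change.** In 9.2, replace the McNemar sentence, and align 9.3.1 and 9.3.2 with it, along these lines: *Non-inferiority is concluded, separately for sensitivity and for specificity, when the lower limit of the confidence interval for the paired difference (Epi proColon minus FIT) lies above -0.20. The interval is a paired one, such as the Tango score interval; the equivalent margin-shifted paired score test may be reported.*

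State the sidedness of the 0.05. The two-sided 95% interval already promised corresponds to one-sided 0.025; if one-sided 0.05 is meant, say so and use the matching 90% interval. The choice of score method is a recommendation; a Wald limit also held 2.4% to 3.0% at the margin for discordant shares of 0.30 to 0.60.

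Keep McNemar's test only for the secondary superiority analysis in 9.4.

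Cost: a few sentences in 9.2 and 9.3 and standard software. The sample size is already described as margin-based, so this change needs no extra subjects.

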### **9.3 Hypothesis Acceptance / Validity Criteria**

#### **9.3.1 Sensitivity for colorectal cancer**

Test performance of the Epi proColon test is considered non-inferior to FIT in CRC subjects, if the sensitivities of Epi proColon and FIT (both relative to reference standard medical diagnosis/colonoscopy) are determined to be equivalent by showing a difference no greater than 0.20 in the two sensitivities.

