#### **9.3.2 Specificity for subject without evidence of disease**

Test performance of the Epi proColon test is considered non-inferior to FIT in NED subjects, if the specificities of Epi proColon and FIT (both relative to reference standard medical diagnosis/colonoscopy) are determined to be equivalent by showing a difference no greater than 0.20 in the two specificities.

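### The pass rule in 9.3 does not tie the 0.20 margin to a confidence bound or a margin-shifted paired test, mixes equivalence with non-inferiority, and is not repaired by 9.2

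*Protocol*

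**What the plan says.** **Acceptance criteria (Protocol 9.3).** Section 9.3.1 states the conclusion first: "Test performance of the Epi proColon test is considered non-inferior to FIT in CRC subjects". The condition is that the sensitivities, each against colonoscopy or medical diagnosis, "are determined to be equivalent by showing a difference no greater than 0.20 in the two sensitivities". Section 9.3.2 repeats this for subjects without evidence of disease: the specificities pass if they "are determined to be equivalent by showing a difference no greater than 0.20 in the two specificities". Neither section names a confidence limit, a test, an error rate or the sign of the difference.

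**Inference and sample size (Protocol 9.2).**
- Sensitivities are to be compared for non-inferiority. For specificity the text reads "Likewise the specificities of Epi proColon and FIT will be compared to establish equivalence". The sample-size paragraph then treats both comparisons as non-inferiority tests for correlated proportions.
- Non-inferiority "will be evaluated using a McNemar's test with type I error rate 0.05". Whether this is one-sided or two-sided is not stated.
- "For both sensitivity and specificity differences 95% confidence intervals will be provided". No sentence says that a limit must clear the margin.
- The largest allowable difference, Epi proColon compared to FIT, "that still results in non-inferiority (non-inferiority margin) is 0.20".
- "With a type I error rate of 5% and 80% power a sample size of 100 subjects per Group would be required".

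Section 3.1 gives the objective as non-inferiority. Section 9.4 adds a superiority test as a secondary analysis.

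**The concern.** A non-inferiority claim at a 5% error rate needs a rule that uses the sampling error of the difference: either a confidence limit that must clear the margin, or a paired test whose null is the margin. Section 9.3 has neither. Section 9.2 names a test whose null is zero difference, so neither a significant nor a non-significant McNemar result answers whether the loss is below 0.20. Two competent statisticians could take these sections and apply different rules to the same data.

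At stake is the success criterion for both primary comparisons, in a study that section 2.2 says is meant to support the device's intended use. The margin is wide, so it matters a great deal whether 0.20 limits the estimate or the bound. Equivalence and non-inferiority are also different hypotheses with different power, and for specificity 9.2 uses both.

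**Working it through.** **Inputs from the protocol.** Margin 0.20, error rate 5% (sidedness not stated), power 80%, 100 evaluable subjects per group, attrition 50%, both tests done in each subject. **Not given:** the FIT rates, the assumed true difference and the proportion of discordant pairs. The discordance values below are assumptions, shown over a range.

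**1. The plan's own figures.** Enrolment reproduces: 100/(1 − 0.5) = 200. The 100 can be neither reproduced nor refuted, because discordance is missing. With n = (z_α + z_β)² ψ / 0.20² at zero true difference (ψ = discordant proportion), n = 100 implies:
- one-sided 5%: ψ = 100 × 0.04 / (1.645 + 0.842)² = about 0.65
- one-sided 2.5%: ψ = 100 × 0.04 / (1.960 + 0.842)² = about 0.51

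So 80% power holds up to those discordances, depending on the level meant.

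**2. Section 9.3 applied to the point estimate.** In Group A let b be the pairs positive on FIT only and c the pairs positive on Epi proColon only. At a true loss of exactly 0.20, their probabilities are (ψ + 0.20)/2 and (ψ − 0.20)/2. The rule passes if (b − c)/100 ≤ 0.20. Exact trinomial enumeration at n = 100 gives:

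| ψ (assumed) | P(pass), observed loss ≤ 0.20 | P(pass), score bound, one-sided 5% | P(pass), score bound, one-sided 2.5% |
|---|---|---|---|
| 0.21 | 0.557 | 0.049 | 0.021 |
| 0.30 | 0.541 | 0.050 | 0.024 |
| 0.40 | 0.533 | 0.049 | 0.024 |
| 0.50 | 0.528 | 0.050 | 0.025 |
| 0.60 | 0.524 | 0.051 | 0.026 |

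The first result column hardly depends on ψ. The row ψ = 0.50 corresponds, for example, to true sensitivities of 0.50 and 0.70 with independent errors: 0.70 × 0.50 + 0.50 × 0.30 = 0.50. The same arithmetic applies to specificity in Group B.

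**3. One data set, two answers.** Take b = 28 and c = 8 of 100. The observed difference, Epi proColon minus FIT, is (8 − 28)/100 = −0.20, which meets 9.3 read literally. The 95% paired score interval (Tango) is −0.31 to −0.09, so a loss well beyond the margin is not excluded. The ordinary exact McNemar test of b = c gives p = 0.001. The test named in 9.2 would find Epi proColon significantly worse, while 9.3 would call it non-inferior.

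**4. How far the readings differ.** Read literally, an observed loss of up to 20 points passes. If the 95% limit must clear the margin (normal approximation), the largest observed loss that passes is about 11 points at ψ = 0.20 and about 6 points at ψ = 0.50.

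**5. Equivalence against non-inferiority.** If n = 100 gives exactly 80% power for non-inferiority at one-sided 5% and zero true difference, two one-sided tests for equivalence have 2 × 0.80 − 1 = 0.60.

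**The case against.** The best defence is that 9.3 should not be read alone. It never says that the observed difference decides. Section 9.2, directly before it, sets a 0.05 error rate, promises 95% intervals, calls 0.20 a non-inferiority margin and gives a direction. On that view 9.2 supplies the inference and 9.3 merely restates the margin. Any point-estimate rule passes about half the time at its margin, so the 52% to 56% shows what that rule would do, not that it will be used.

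Much of this stands, and it rules out two stronger readings.
- A reader might infer that the trial's error rate simply is about one half. The documents do not support that: the figure follows from one literal reading of 9.3, and that reading conflicts with the 0.05 in 9.2.
- A reader might infer from the unsigned wording that Epi proColon would fail if it beat FIT by more than 0.20. The objective in 3.1, the directional margin in 9.2 and the planned superiority test in 9.4 all point the other way.

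Likewise, most of the text treats specificity as non-inferiority, so the equivalence sentence looks like loose wording rather than a second planned analysis. The 60% in step 5 shows only what that wording would cost if taken at its word.

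What the defence does not do is produce a decision rule. The intervals are reported without a role, McNemar's test as named does not test 0.20, and sidedness is missing. Nor is this an ordinary deferral to the SAP. Section 9.1 leaves data displays to it, whereas 9.3 fixes the acceptance criterion in the protocol itself, and an SAP rule based on a bound would then depart from that text.

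**Conclusion.** The point holds as a defect in how the success criterion is specified. Sections 9.2 and 9.3 together do not determine one rule for either primary comparison, and their literal contents can give opposite answers on the same data. If the point estimate is used, the chance of passing at a true loss of 0.20 is 52% to 56% per endpoint at n = 100, against the stated 5%. That size is conditional on this reading and on assumed discordance of 0.60 to 0.21, though it varies little over that range. The stated sample size is not shown to be wrong. It should be corrected before the results are known, because the choice of reading can decide the outcome.

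**What to change.** **9.3.1 and 9.3.2.** State that non-inferiority is shown, for each endpoint, if the lower confidence limit (paired score method) for Epi proColon minus FIT exceeds −0.20. State the one-sided level: 5% (a 90% interval) or 2.5% (the 95% interval already planned).

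**9.2.** For the non-inferiority question, replace McNemar's test with this bound or with a paired test shifted to the margin. Keep the ordinary McNemar test for the secondary superiority analysis in 9.4.

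**Wording.** Replace equivalent and equivalence with non-inferior and non-inferiority in 9.2, 9.3.1 and 9.3.2.

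**Cost.** A few sentences, and a rule stricter than the literal text. The level also affects power. If 100 per group was sized for exactly 80% at one-sided 5%, the 95% interval gives Φ(2.486 − 1.960), about 70%. The power statement in 9.2 must therefore be matched to the chosen level, with the assumed discordance given. At zero true difference no extra subjects are needed up to a discordance of about 0.65 (one-sided 5%) or 0.51 (one-sided 2.5%).

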#### **9.3.2 Specificity for subject without evidence of disease**

Test performance of the Epi proColon test is considered non-inferior to FIT in NED subjects, if the specificities of Epi proColon and FIT (both relative to reference standard medical diagnosis/colonoscopy) are determined to be equivalent by showing a difference no greater than 0.20 in the two specificities.

